### Sample size

Primarily this study sets out to assess whether, 6 weeks after onset of treatment the Numerical Pain Rating Scale NPRS score in the intervention group is reduced compared to the UC group. A blocked 2:1 ratio randomisation for intervention to usual care will be done using a computer generated random number list. A sample size of 68:34 i.e. a total sample of 102 patients will have 90% power to detect a clinically relevant increase of 2 for the change from baseline at six weeks in the NPRS score. A standard deviation of 2.05 was assumed as derived from the effect size reported by Bolton and Wilkinson [42]. The standard deviation was furthermore inflated by √2 since change from baseline is of interest. A dropout rate of 15 – 20% was assumed. One-sided testing will be done at the 0.05 level of significance. (nQuery advisor 7).

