### Outcome measures

The treating physiotherapist will administer the first set of questionnaires. Treatment randomisation will only be done as described above, after initial measures have been taken. All subsequent follow up questionnaires will be administered by a research assistant who will be blinded to group allocation as the follow up questionnaires at three weeks and six weeks will be done telephonically. The primary outcomes are pain (Numeric Pain Rating Scale), function (Patient Specific Functional Scale) and quality of life (EuroQual Instrument). These self-report outcomes will be followed up at three weeks, six weeks, six months and 12 months.

The NPRS will be used to measure the patient’s pain. The NPRS is an 11-point scale where patients are asked to rate their pain as 0 representing “no pain” and 10 “worst pain possible”. In a study comparing three pain measures [42]. Bolton and Wilkinson [42] found the NPRS to be the most responsive pain measure with an effect size of 0.86 [42]. The validity of the NPRS in an acute setting was established by Bijur et al. [43] and is strongly correlated with the visual analogue scale (r = 0.94, 95% Confidence Interval 0.93 – 0.95) [43]. The NPRS is as sensitive to change as the visual analogue scale which is currently considered the “gold standard” [44].

The Patient Specific Functional Scale (PSFS) will be used to measure disability. The PSFS is a self-report measure to rate activity limitation and function. Patients are asked to nominate three to five activities that are difficult to perform and rate them on an 11 point scale where 0 equals “unable to perform activity” and 10 represents “able to perform activity as before”. The scale was initially developed for patients with back pain and validated for patients with neck pain by Westaway et al. [45]. The scale has excellent validity (r = 0.73 - 0.83) when compared to the Neck Disability Index [45]. The test retest reliability coefficient is excellent (ICC = 0.97) [46]. Cleland et al. [47] compared the Neck Disability Index (NDI) and the PSFS in patients with cervical radiculopathy and found that the PSFS was more responsive than the NDI in this population [47]. In their study the test-retest reliability coefficient was good (ICC 0.82). The scale is commonly used in physiotherapy practice [48].

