### Statistical considerations

Primarily this study sets out to assess whether, six weeks after onset of treatment the NPRS score in the intervention group is reduced compared to the UC group. The sample size calculation is reported for the NPRS, which require the largest sample size.

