### Data analysis

The data summary will employ descriptive statistics, means, standard deviations and 95% confidence intervals and will be reported by study group (intervention & standard care) for the NPRS, PSFS and EQ-5D. Catastrophising (yes & no) and neuropathic pain (yes & no) will be summarised using frequencies, percentages, cross tables and 95% confidence intervals.

Two treatment groups will be compared with respect to the change from baseline at six weeks in the NPRS, PSFS and EQ-5D scores using an analysis of covariance (ANCOVA) with baseline scores, catastrophising (yes & no) and neuropathic pain (yes & no) as covariates. For the total assessment period of 12 months the interaction between visits and treatment will be assessed with respect to NPRS, PSFS and EQ-5D scores in a linear mixed model analysis. Testing will be done at the 0.05 level of significance. For all data description and analyses an intention-to-treat analysis will be performed.

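### The only inference named for the 12-month period is the visit-by-treatment interaction, with baseline's role left open, and its p-value alone cannot show whether a benefit lasts

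*Protocol article*

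**What the plan says.** The Outcome measures section sets the schedule for pain (NPRS), function (PSFS) and quality of life (EQ-5D): "These self-report outcomes will be followed up at three weeks, six weeks, six months and 12 months".

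The Data analysis section then uses two methods.

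- **Six weeks.** "Two treatment groups will be compared with respect to the change from baseline at six weeks in the NPRS, PSFS and EQ-5D scores". This is an ANCOVA with baseline score, catastrophising and neuropathic pain as covariates. It serves the stated primary question, in which usual care is the comparator: "Primarily this study sets out to assess whether, six weeks after onset of treatment the NPRS score in the intervention group is reduced compared to".
- **Twelve months.** "For the total assessment period of 12 months the interaction between visits and treatment will be assessed", and this is done "with respect to NPRS, PSFS and EQ-5D scores in a linear mixed model analysis".

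The second method is applied to scores, whereas the first is applied to change from baseline. The section does not say whether the baseline score is one of the repeated scores in the mixed model, a covariate, or left out. It names no treatment effect averaged over follow-up and no between-group difference at any visit after six weeks. Means, SDs and 95% confidence intervals are promised by study group, which is not an estimate of the difference between groups.

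**The concern.** The first aim is the effect of neural mobilisation on pain, function and quality of life, and all three are followed to 12 months. A reader will want to know whether patients given neural mobilisation are better off at six and 12 months, and by how much. A visit-by-treatment interaction asks something else: whether the between-group difference is the same at every visit in the model. What a significant or non-significant result means depends on which visits are in the model, and the article leaves that open.

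At stake is the long-term conclusion. A non-significant interaction could be read as no lasting effect when the effect is constant. A significant one could be read as lasting effect when an early benefit has disappeared.

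**Working it through.** **Inputs from the Sample size section.** SD 2.05 at a single visit, target difference 2 points, 2:1 allocation, one-sided 0.05, 90% power, dropout 15-20%. The SD for change is 2.05 × √2 = 2.899, which implies a correlation of 0.5 between visits.

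**The plan's own figure.** Control group: (1 + 1/2) × 2.899² × (1.645 + 1.282)² / 2² = 27, so 54:27 = 81 evaluable. Then 81/0.80 = 101.25, which rounds up to 102 in a 2:1 split. The stated 68:34 is reproduced at 20% dropout. It does not bear on this point except as the source of 54:27.

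**Assumptions added here.** SD 2.05 at every visit; equal correlation ρ between visits, shown for 0.3 to 0.5 because the article gives no value; 54:27 patients at every visit; two-sided 0.05; large-sample chi-square tests.

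**Formula.** Let d_j be the true between-group difference at visit j. With equal correlation, the noncentrality of the interaction test is

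λ = Σ(d_j − mean d)² / [SD² × (1 − ρ) × (1/27 + 1/54)],

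with 3 df for the four follow-up visits and 4 df if baseline is a fifth visit. Here SD² × (1/27 + 1/54) = 4.2025 × 0.05556 = 0.2335, so the denominator is 0.1634 at ρ = 0.3 and 0.1167 at ρ = 0.5.

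**A 1-point benefit, two patterns over time.** Sustained means 1 point at all four follow-ups. Vanished means 1 point at three and six weeks and none at six and 12 months.

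| Visits in model | Pattern | Σ(d_j − mean d)² | λ (ρ = 0.3; 0.5) | Chance of p < 0.05 |
|---|---|---|---|---|
| Follow-ups only, 3 df | Sustained | 0 | 0; 0 | 5% |
| Follow-ups only, 3 df | Vanished | 1.0 | 6.12; 8.57 | 53-69% |
| Baseline included, 4 df | Sustained | 0.8 | 4.90; 6.85 | 39-53% |
| Baseline included, 4 df | Vanished | 1.2 | 7.34; 10.28 | 56-73% |

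The ordering does not depend on ρ or on the size of the benefit. The sums of squares stay in the ratio 0 to 1.0 in one reading and 0.8 to 1.2 in the other.

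**Sustained benefit at other sizes.** With follow-ups only, the rejection rate stays at 5% for any size. With baseline included, λ grows with the square of the benefit: power is 76-90% at 1.5 points and 96-99% at the design difference of 2 points. Over a wider correlation range of 0 to 0.7, it is 86-100% at 2 points and 28-78% at 1 point.

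**Comparison with a direct contrast.** A baseline-adjusted difference at one visit has standard error 2.05 × √(1 − ρ²) × √(1/27 + 1/54), which is 0.461 at ρ = 0.3 and 0.419 at ρ = 0.5. Its power is 58-67% at 1 point and 90-95% at 1.5 points. It is the same for any single visit and answers the question for that visit.

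**The case against.** The strongest reply is that baseline is naturally one of the visits. The article moves from change scores at six weeks to scores over the whole assessment period, so the repeated scores may well start at baseline. The between-group difference then goes from about zero to d, and a sustained benefit is itself an interaction. At 2 points and ρ = 0.5 the 4-df test has 99.4% power, slightly more than the 98.5% of an unadjusted 12-month change contrast. This stands. A reader might infer that the interaction can never detect a lasting effect; the text does not support that, because it does not exclude baseline.

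Second, asking whether an effect established at six weeks changes later is a coherent secondary question, and a vanished benefit giving a significant interaction is the test working as it should. That also stands. It does not turn the p-value into evidence of a lasting effect, and no other long-term inference is named.

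Third, visit-specific contrasts may be in an analysis plan that is not shown. They may, so their absence from the article is not itself the fault. The point rests on the test the article does name, and on its leaving unstated what that test means.

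Two stronger readings are tempting. One is that the six-week result is compromised. It is not: it comes from a direct between-group ANCOVA, separate from the interaction. The other starts from "For all data description and analyses an intention-to-treat analysis will be performed" and "A dropout rate of 15 – 20% was assumed" and infers that the ANCOVA will in fact be a completers' analysis. The article nowhere says that patients without a six-week score are dropped, and handling of missing data is commonly left to the analysis plan. Nor does the wider worry about an unblinded comparison fit without qualification: the research assistant who administers the follow-up questionnaires is blinded to group.

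**Conclusion.** The point holds for the 12-month analysis only. As written, the named test has two readings with very different properties. With follow-up visits only, a sustained benefit of any size is picked up no more often than chance. With baseline as a visit, detection is good at the design difference and modest at half of it, but the 4-df result gives neither the visit nor the direction.

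Under both readings, an early benefit that disappears is more likely to be significant than the same benefit sustained. At 2 points with baseline included, this ordering hardly matters for power, since a sustained benefit is already flagged 96-99% of the time; there the difficulty is that significance does not tell the two patterns apart. The interaction p-value alone therefore cannot support a conclusion about lasting effect.

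The percentages rest on equal correlation of 0.3 to 0.5, a constant SD of 2.05 and 54:27 patients at every visit. The zero interaction for a constant effect across follow-up visits needs none of these. This is worth correcting, but it concerns secondary time points and leaves the primary comparison intact.

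**What to change.** Keep the six-week ANCOVA as the primary analysis. For the 12-month mixed model:

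1. State how baseline enters: either as a covariate, with its interaction with visit and with catastrophising and neuropathic pain as in the ANCOVA, or as a visit at which the two group means are constrained to be equal.
2. Pre-specify the between-group difference with a 95% confidence interval at each follow-up visit, in particular six and 12 months, as the long-term result for each outcome.
3. Use the visit-by-treatment interaction only to describe whether the effect changes over time.

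The model is already planned and no new data or patients are needed. The cost is a little more analysis and reporting: four differences for each of three outcomes, 12 in all, with those other than at six weeks labelled as secondary.

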## Discussion

Evidence for the treatment of neck and arm pain (including radiculopathy) is sparse [28]. In a recent review of non-invasive treatment for cervico-brachial pain, Salt et al. [6] found inconclusive evidence for the effectiveness of treatment on pain. Potential benefit was found for manual therapy, exercise and behavioural change approaches. The effect of treatment on function in this population group was mixed. They recommend that studies investigate which subgroups of patients will respond to specific interventions. It is postulated that mechano sensitivity of the nerves plays a role in cervico-brachial pain [8, 9] In this study the effect of neural mobilisation on a population with cervico-brachial pain and nerve mechano-sensitivity will be investigated. Clinical reasoning suggests that targeting the neural structures in these patients could be beneficial.

## Conclusion

The findings of this study should add to the knowledge base on the management of patients with cervico-brachial pain. Results of this study will be published in an appropriate journal.

## Authors’ original submitted files for images

Below are the links to the authors’ original submitted files for images. Authors’ original file for figure 1
